### Preconception weight loss to reduce gestational diabetes and associated health risks

Observational research suggests that women who experience even modest weight losses (> 10 pounds) [33, 34, 83] or less weight gain [84–86] prior to pregnancy significantly reduce their risk of GDM development compared to women who maintain weight or gain > 10 pounds. Kim et al. [48] estimated that up to half of GDM cases could be prevented by reducing pre-pregnancy obesity. Retrospective data from bariatric surgery populations also suggest that weight loss in women with obesity prior to pregnancy may reduce the risk of GDM and its recurrence [37, 87, 88] and prevent transmission of obesity to children [36]. Other observational research has shown that maternal consumption of healthy food and avoidance of unhealthy foods [89] and engagement in regular physical activity before pregnancy were independently associated with reduced risk of subsequent GDM [89]. Honein et al. [90] estimated that if 10% of women with pre-pregnancy obesity achieved a healthy weight (BMI < 25) before pregnancy, nearly 300 congenial heart defects and 700 fetal deaths per year could be prevented each year.

However, few clinical trials have examined the effects of weight loss during the preconception period on subsequent outcomes [41, 91]. The PREPARE randomized trial [41] tested a phone-based weight loss intervention in 326, non-Hispanic (94%) women with a BMI ≥ 27 and found that, relative to the control group, women in the lifestyle intervention lost more weight prior to conception (3.7 vs. 0.6 kg, respectively). After 24 months, 169 (52%) became pregnant and were included in the analysis. The results indicated that those in the preconception intervention group surprisingly gained more weight during their subsequent pregnancy than those in the control group (13.2 vs. 10.3 kg gain, respectively; *p =* 0.03); there were no significant differences in GDM or other pregnancy outcomes, with the exception of spontaneous pregnancy losses, which were less common in the intervention arm. Participants in the intervention arm had a 10% lower absolute rate of GDM than in the control arm (25% vs. 35%, respectively), but the study had insufficient power to evaluate whether or not a difference of this size was due to chance.

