### Objectives {7}

The Gestational Diabetes Prevention/Prevención de la Diabetes Gestacional is a two-site randomized clinical trial testing the efficacy of a pre-pregnancy lifestyle intervention to reduce GDM recurrence in women with overweight and obesity. The trial is following the CONSORT guidelines [103]. The primary hypothesis is that the recurrence of GDM will be reduced among participants assigned to pre-pregnancy lifestyle intervention vs. educational control group. Test for GDM will be conducted at 24 to 28 weeks’ gestation. Secondary hypotheses are that the pre-pregnancy lifestyle intervention (vs. educational control group) will result in improved maternal fasting glucose and biomarkers of insulin resistance (insulin, leptin, TNF-alpha, C-reactive protein, and adiponectin) and CVD risk (lipids and blood pressure) assessed before pregnancy, after 16 weeks of intervention, and at 26 weeks’ gestation. The pre-pregnancy lifestyle intervention (vs. educational control group) is expected to reduce adverse perinatal health outcomes for mothers (gestational hypertension, preeclampsia, preterm delivery, excessive gestational weight gain, induction of labor, cesarean delivery) and neonates (admission to the neonatal nursery, hyperbilirubinemia, birth trauma, weight for length *z*-scores ≥ 95% at birth and 6 weeks). Also, the pre-pregnancy lifestyle intervention (vs. educational control group) is hypothesized to result in greater pre-pregnancy weight loss and improvements in diet (calories, % fat, fast food) and physical activity (minutes of moderate activity). In exploratory mediator analyses, treatment-related changes in pre-pregnancy weight, eating, and activity are expected to be related to improvements in maternal physiology and reduced odds of GDM recurrence.

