#### Group 2: Standard care + education + weight loss intervention

##### Overview

This group receives all aspects of group 1 plus a standard lifestyle modification program implemented to induce ≥ 10% weight loss over 16 weeks and promote weight loss maintenance over subsequent months (12–36 months depending on enrollment year) until conception. This comprehensive, individually focused, SCT-based weight control program includes education, behavioral self-regulatory strategies, ongoing contact, feedback, and social support. The intervention is based on the DPP and Look Ahead lifestyle interventions [101, 119, 120], which have been proven effective in promoting significant weight loss and maintenance in multiethnic, English- and Spanish-speaking individuals across the country [119, 120]. The intervention provides guidance and resources for English- and Spanish-speaking individuals from a variety of different cultures and backgrounds.

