### Participant timeline {13}

Table 3 shows when participants complete the measures in Gestational Diabetes Prevention/Prevención de la Diabetes Gestacional. Bilingual (English/Spanish-speaking) assessors are masked to randomization and conduct all major assessments occurring at baseline, after 16 weeks, at 26 weeks’ gestation, and at 6 weeks postpartum. These assessments occur at the study’s research centers or affiliate locations most proximal to participants. If necessary, assessments are conducted at participants’ homes. After 16 weeks, quarterly brief assessments occur until conception. The brief assessments may be conducted in person or over the phone/video conferencing.

**Table 3 Tab3:** Measures in Gestational Diabetes Prevention/Prevención de la Diabetes Gestacional

	Assessment time point				
	Pre-pregnancy			Pregnancy	Postpartum
	Baseline	4 months	Every 4 months until pregnancy	26 weeks’ gestation	6 weeks
Demographics and medical history	X	X	–	X	X
Weight, height, waist circumference	X	X	X	X	X
Pregnancy test	X	X	X	–	–

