## Statistical methods

### Statistical methods for primary and secondary outcomes {20a}

A multiple logistic regression analysis will be used to examine the effect of the treatment group on the proportion of women who develop GDM. The model will include site and covariates to adjust for pre-randomization variables that may relate to the outcome, including parity, age, education, income, smoking, race/ethnicity, BMI, and time since last pregnancy. The effects of the pre-pregnancy weight loss intervention on weight, eating, activity, and physiologic outcomes will be examined using a linear mixed model with fixed effects for treatment condition (the between-groups factor), time (baseline, 16 weeks, 26 weeks’ gestation), site, and baseline covariates. Linear regression and logistic regression analyses will be performed to address the possible effects of the intervention on cases of excessive GWG, gestational hypertension, cesarean delivery, and large for gestational age at birth and 6 weeks, with site and baseline covariates entered in the models. A multiple linear regression analysis will also be used to examine the effect of the treatment group on composite scores of adverse maternal/neonatal outcomes, and logistic regressions will be used to examine separate effects on offspring obesity and odds of exceeding the National Academy of Science guidelines, including the same covariates described above.

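### The weight model compares the groups before pregnancy only at week 16; the scheduled weights from then to conception enter no treatment comparison

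*Protocol article*

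**What the plan says.** Protocol article, Statistical methods for primary and secondary outcomes {20a}: "The effects of the pre-pregnancy weight loss intervention on weight, eating, activity, and physiologic outcomes will be examined using a linear mixed model". The model's time factor is given as "time (baseline, 16 weeks, 26 weeks’ gestation"). One list of time points serves all four groups of outcomes.

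Participant timeline {13}, Table 3: the row "Weight, height, waist circumference" is marked at baseline, 4 months, 26 weeks' gestation and 6 weeks postpartum, and also in the column "Every 4 months until pregnancy". The text of that section agrees: "After 16 weeks, quarterly brief assessments occur until conception". Those brief visits may be in person, by phone or by video.

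Objectives {7}: the intervention "is hypothesized to result in greater pre-pregnancy weight loss". The Overview of the Group 2 intervention sets a target at 16 weeks and then aims to "promote weight loss maintenance over subsequent months (12–36 months depending on enrollment year) until conception". Sample size {14} makes pre-pregnancy weight loss the subject of the fourth aim.

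A pre-pregnancy weight appears in two other places. The additional analyses {20b} relate pre-pregnancy change in weight to GDM recurrence as exploratory mediation, with no time point given. The section on maternal and infant consequences uses a measured pre-pregnancy weight as the starting point for gestational weight gain.

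**The concern.** The three time points suit diet, activity and physiology, which Table 3 schedules mainly at those visits. They do not suit weight, which has a fuller schedule and a different aim. The intervention has two phases, loss to week 16 and then maintenance until conception. The stated model compares the groups at the end of the first phase and does not touch the second.

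The weight a woman carries into pregnancy is the quantity the trial's rationale depends on. If the groups drift together after week 16, or apart, the planned comparison will not show it. The protocol notes a similar gap in the Finnish preconception trial, where weight change before conception went unanalysed and GDM rates did not differ. A null GDM result here would be harder to interpret without a planned comparison of weight close to conception.

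The 26-week weight cannot fill the gap. It mixes what was lost before pregnancy with what was gained during it, and it is available only for women who conceive.

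**Working it through.** The plan states no figure for this point, so there is none to reproduce. The check compares schedule with model, and then uses the protocol's own background figures as an illustration.

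**1. Schedule against model (weight only)**

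| Time point | Scheduled in Table 3 | In the {20a} model |
|---|---|---|
| Baseline | yes | yes |
| 4 months / 16 weeks | yes | yes |
| Every 4 months until pregnancy | yes | no |
| 26 weeks' gestation | yes | yes |
| 6 weeks postpartum | yes | no |

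The only post-baseline, pre-pregnancy weight in the model is the one at 16 weeks.

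**2. How old that weight is at conception**

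Input: 4-monthly visits from Table 3. Assumed conception times are 12, 24 and 36 months after entry, spanning the 1–3 year planning window. For conception at month c, the last modelled pre-pregnancy weight is c − 4 months old. Unused visits fall at months 8, 12, … up to c − 4, so there are (c − 8)/4 of them.

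- c = 12: 12 − 4 = 8 months old; (12 − 8)/4 = 1 weight unused.
- c = 24: 24 − 4 = 20 months old; (24 − 8)/4 = 4 unused.
- c = 36: 36 − 4 = 32 months old; (36 − 8)/4 = 7 unused.

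A woman who conceives before month 8 loses no scheduled weight.

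**3. Who can have a 26-week weight**

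Inputs from Sample size {14}: 252 randomised, 70% pregnant. 252 × 0.70 = 176.4, so 176, or 88 per group, as the protocol states. On that assumption 252 − 176 = 76 randomised women would have no 26-week weight. They could still have weights after week 16.

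**4. Why a pregnancy weight is not a substitute (illustration only)**

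Inputs from the phone-based preconception trial described in the background: loss before conception 3.7 vs 0.6 kg, after which the intervention group "gained more weight during their subsequent pregnancy than those in the control group (13.2 vs. 10.3 kg gain").

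- Difference before conception: 3.7 − 0.6 = 3.1 kg in favour of intervention.
- Difference in gestational gain: 13.2 − 10.3 = 2.9 kg the other way.
- Net by the end of pregnancy: 3.1 − 2.9 = 0.2 kg.

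The share of that 2.9 kg present by 26 weeks is not in the documents. Assuming 40% to 70%:

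- 40%: 3.1 − 0.4 × 2.9 = 1.94 kg
- 70%: 3.1 − 0.7 × 2.9 = 1.07 kg

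On those assumptions a 26-week contrast would understate the difference carried into pregnancy by 1.16 to 2.03 kg. This shows that the two weights measure different things. It does not measure what is lost by leaving out the 4-monthly weights; the documents give no figure for regain after week 16.

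**The case against.** The strongest reply is that the list of time points is shared across several outcomes and follows the major masked assessments, and that a condensed article may leave weight-specific visits to a fuller plan. That would carry weight if the article were silent. It names weight as an outcome of this model and lists the levels, so this is a stated choice that fits the aim poorly.

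Four further points stand and limit the finding.

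- Pre-pregnancy weight loss is analysed at week 16, which is the intervention's own target date. A reader might infer that it is not analysed at all; that is wrong.
- A reader might infer that the trial could never say anything about weight at conception. The documents do not support that either. The weights are scheduled, a mediator analysis of pre-pregnancy weight change is planned, and a measured pre-pregnancy weight is expected for gestational gain. But the mediator analysis is exploratory, gives no time point and relates weight to GDM. Neither use compares the groups on weight near conception.
- The 0.2 kg net figure invites the conclusion that over 90% of the effect would vanish here. It comes from another trial, and the background text does not establish that the loss and the gain were measured in the same women. A 26-week weight obscures the 16-week contrast only if the two are averaged. That depends on whether the model has a treatment-by-time term, which is a separate matter.
- Changing the wording alone is not enough. Brief-visit weights may be self-reported, and a supplied scale is mentioned only for the intervention group, so measurement could differ by arm. A last pre-conception weight exists only for women who conceive.

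**Conclusion.** The point holds in this form: the stated weight model gives one pre-pregnancy treatment contrast, at week 16, although the aim extends to conception and weights are scheduled throughout. No planned between-group comparison covers the time from week 16 to conception. In the illustration, that leaves the last modelled pre-pregnancy weight 8 to 32 months old for conceptions at 12 to 36 months, with one to seven scheduled weights unused.

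The effect on the weight estimate in this trial cannot be sized from the documents. The conclusion rests on reading the listed time levels as written and on the 4-monthly visits taking place as scheduled. It concerns a secondary outcome and the mediator; the primary GDM comparison is unaffected. It should be corrected because it is cheap to do so and bears directly on how the GDM result will be explained.

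**What to change.** In {20a}, separate weight from the other outcomes of the mixed model:

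- Fit the pre-pregnancy weight model to baseline, 16 weeks and every scheduled 4-monthly weight, in all randomised women, censoring at conception. Any weight taken after conception is left out. Let the treatment effect vary by visit so that it can be read after week 16.
- Report 26-week weight separately, as a weight in pregnancy.
- In {20b}, define the weight mediator as change from baseline to the last weight before conception. Report the same change as a secondary between-group contrast among women who conceive, stating that this subset is formed after randomisation and is not a fully randomised comparison.
- Record for each weight whether staff measured it or the woman reported it, and repeat the analysis with staff-measured weights only.

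The cost is small: no added visits or participants, but a rule for dating conception, a source flag and one sensitivity analysis. Two limits remain. Self-reported weights may differ in error between the arms. Censoring at conception also relies on the weights already observed to account for who conceives early.

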#### Infant measures

At 6 weeks, infant length, weight, and skinfold thickness measurements are performed by trained staff using standardized procedures. BMI *z*-scores are calculated using the WHO Child Growth Standards for age and sex [147]. A *z*-score of > 1 will be used to define at risk for obesity.

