### Sample size {14}

Power calculations assume a 60% GDM recurrence rate in women with overweight or obesity [19, 57, 58]. With a target sample size of 252 participants and assumed ≥ 70% pregnancy rate [151, 152] and 30% lost to follow-up or not pregnant before conception, ≥ 176 pregnant participants (≥ 88 in each group) would provide adequate statistical power (≥ 81.98%) to detect intervention effects on the proportions developing recurrent GDM [83, 153], taking into account estimations of site-specific clustering effects and effect modifiers (i.e., weight status, ethnicity, parity) of GDM recurrence [24, 57]. Under this scenario, the minimum detectable effect size (odds ratio) would be 0.43, and proportions with GDM in educational control and intervention groups respectively would be 60% (*n* = 53/88) and 38% (*n* = 33/88). For secondary aims, 88 pregnancies in each group would yield > 80% power to detect effects equal to or smaller than those reported in prior work testing effects of lifestyle interventions on reductions in glucose, triglycerides, CRP [154], insulin, leptin [155], adiponectin [156], and blood pressure [157], taking into account estimations of site-specific clustering effects and effect modifiers (i.e., weight status, ethnicity, parity) of insulin resistance [158], and CVD risk factors [159, 160]. For secondary aims examining effects of the intervention on prenatal and perinatal complications, the study would have > 80% power to detect moderate effect sizes [161]. For the fourth aim examining the effects of the intervention on pre-pregnancy weight losses and improvements in eating (calories, macronutrient balance, fast food) and activity, 88 participants in each group would yield > 90% power to detect effects reported in prior work testing effects of lifestyle interventions on reductions in weight [157] and behavioral variables [162, 163]. For exploratory mediator analyses, > 80% power is achieved to detect > 21% increase in the mediated odds of GDM per kilogram difference in pre-pregnancy weight loss (equivalent to a mediated slope in a logistic model of > 0.189).

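### The only stated use of the 6-week infant BMI z-score is a cut at z > 1; a linear analysis of the score alongside it would recover power at almost no cost

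*Protocol article*

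**What the plan says.** Under Outcomes {12}, Infant measures, the protocol article describes the 6-week visit, where "infant length, weight, and skinfold thickness measurements are performed by trained staff using standardized procedures". Body mass index is then put on a continuous standardised scale, on which "scores are calculated using the WHO Child Growth Standards for age and sex". The threshold of 1 on that scale "will be used to define at risk for obesity". This is the only use of the z-score that the article describes.

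Statistical methods {20a} then states that "logistic regressions will be used to examine separate effects on offspring obesity". The article does not spell out that offspring obesity means z > 1, but that cut is its only definition tied to obesity risk.

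Two other places mention infant size at 6 weeks, and both describe a category:

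- Objectives {7} lists weight-for-length z-scores "≥ 95% at birth and 6 weeks" among the adverse neonatal outcomes.
- {20a} says "Linear regression and logistic regression analyses will be performed to address the possible effects of the intervention on cases of excessive GWG" and, at the end of the same list, "large for gestational age at birth and 6 weeks, with site and baseline covariates entered in the models".

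For maternal weight, eating, activity and physiology, {20a} uses a linear mixed model, so those measures stay on their full scale.

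**The concern.** A measured quantity is reduced to yes or no before the arms are compared. The cut lies in the upper tail, where few infants are expected, so most of the information about a general shift in infant size is lost. The Background gives offspring adiposity as part of the reason for the trial. With at most about 88 infants per arm, a null logistic result on z > 1 would say little about whether infant size had changed. The continuous value is already in hand and the plan uses linear models elsewhere, so the loss is avoidable.

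**Working it through.** **Inputs from the article.** 88 pregnancies per arm (Sample size {14}); 1:1 allocation (Trial design {8}); cut at z > 1 (Infant measures).

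**Assumptions, because the article gives no figure.** Two-sided 5% test; normal z-scores with SD 1 in both arms; control mean 0, so 15.9% of control infants exceed z = 1; downward shift of d SD in the intervention arm. The 88 counts pregnancies, so at the planned sample size it is an upper bound for infants measured at 6 weeks.

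**Check of the method on the plan's own figure.** The article states power of at least 81.98% for GDM of 60% against 38% with 88 per arm. The pooled two-proportion formula gives Φ((0.22 − 1.96 × 0.0754)/0.0735) = Φ(0.98) = 83.7%, within 2 points; Fisher's exact test gives 81.8%. The formulas are therefore on the plan's scale. The article states no power figure for infant size at 6 weeks.

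**Full-scale comparison.** Power = Φ(d√(n/2) − 1.96), with √(88/2) = 6.633.

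**Comparison after the cut.** Control proportion p₁ = 1 − Φ(1) = 0.1587; intervention proportion p₂ = 1 − Φ(1 + d); power = Φ((p₁ − p₂ − 1.96·s₀)/s₁), where s₀ and s₁ are the pooled and unpooled standard errors.

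| Shift d | Full scale | p₂ | s₀, s₁ | After the cut | Loss (points) |
|---|---|---|---|---|---|
| 0.2 | Φ(1.327 − 1.96) = 26.3% | 0.1151 | 0.0518, 0.0517 | Φ(−1.12) = 13.1% | 13.2 |
| 0.3 | Φ(1.990 − 1.96) = 51.2% | 0.0968 | 0.0503, 0.0501 | Φ(−0.73) = 23.2% | 28.0 |
| 0.4 | Φ(2.653 − 1.96) = 75.6% | 0.0808 | 0.0489, 0.0486 | Φ(−0.37) = 35.5% | 40.1 |
| 0.5 | Φ(3.317 − 1.96) = 91.3% | 0.0668 | 0.0477, 0.0472 | Φ(−0.03) = 48.6% | 42.6 |

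(Losses are taken before rounding.)

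**Check by simulation** (20,000 runs, t-test against an unadjusted logistic likelihood-ratio test, cut at z > 1). For d = 0.422: 79% against 39%. For d = 0.489: 89% against 49%. The formula gives 38% and 47% after the cut, so it is close at this cut.

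**Sensitivity to the control mean**, same cut, loss in points:

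| Control mean (share above z = 1) | d = 0.2 | d = 0.3 | d = 0.5 |
|---|---|---|---|
| −0.5 (6.7%) | 17.0 | 36.2 | 62.1 |
| 0 (15.9%) | 13.2 | 28.0 | 42.6 |
| 0.5 (30.9%) | 9.8 | 20.4 | 25.9 |
| 1 (50%) | 8.1 | 16.3 | 17.4 |

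The loss becomes small only where the shift is large and the control prevalence high: for d = 0.8 with control mean 1 it is 1.6 points.

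**Fewer infants.** With 75 per arm and d = 0.5 (control mean 0), power is about 86% on the full scale against 43% after the cut.

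**The case against.** **A linear analysis may already be intended.** The sentence in {20a} that names both linear and logistic regression covers a list ending in size at 6 weeks. Every item as worded is a category, so naming linear regression makes most sense if continuous counterparts are meant. This stands in part: a reader might infer that the z-score is analysed only as yes or no, and the article does not establish that. Equally, the sentence speaks of cases, does not mention the BMI z-score, and is followed by a separate sentence giving offspring obesity to logistic regression.

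**This is a condensed article, and a fuller plan may settle it.** That is possible. The point is not that detail is missing, however: the article itself fixes the measure, the cut and the model. If a fuller plan has the linear model, the edit only brings the article into line.

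**The binary endpoint matches the hypothesis.** Objectives {7} predicts fewer infants in the upper tail. The maternal and infant outcomes under {12} count small size for gestational age as adverse and put birth weight below 2500 g into a composite. A lower mean is therefore not plainly a benefit. This stands, and it is why the z > 1 analysis should be kept and not displaced.

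**The sample-size statement.** A reader might infer that the cut breaks the statement in {14} that "the study would have > 80% power to detect moderate effect sizes". The article does not support that. The sentence concerns prenatal and perinatal complications, does not name 6-week infant size and gives no numeric effect. If moderate means Cohen's h = 0.5 for proportions, power is Φ(0.5 × √44 − 1.96) = Φ(1.36), about 91%, and the statement holds.

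**A larger loss might be quoted.** For a 0.5 SD shift, varying the control prevalence from 50% to 5% gives losses of 17 to 67 points. That range is not a property of the plan. The 5% end borrows the weight-for-length criterion from {7}, a different measure from the BMI z-score. The normal approximation also overstates the loss there: at d = 0.489, simulation gives 90% against 31%, a loss of about 59 points. A 0.5 SD shift is itself unsupported by the article.

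**Small shifts defeat both analyses.** At 0.2 SD the full-scale test has only 26% power. This is true; the linear analysis improves the position without guaranteeing an answer. Its confidence interval would at least show which shifts remain compatible with the data.

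**Conclusion.** The point holds as a minor one. The article computes a continuous z-score, states only a cut for it, and tests offspring obesity by logistic regression; no sentence clearly assigns a model to the score itself. At the article's own cut, the loss is about 13 points of power for a 0.2 SD shift, 28 for 0.3 SD and 43 for 0.5 SD. These sizes rest on 88 infants per arm, normal z-scores with SD 1, a control mean of 0 and a two-sided 5% test. The article supplies neither the shift nor the control prevalence, and other values move the loss as tabulated. The direction does not depend on these choices within the range examined. The outcome is secondary, and the GDM analysis is untouched.

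**What to change.** In {20a}, prespecify a linear regression of the continuous 6-week infant BMI z-score on treatment, site and the same baseline covariates, reporting the mean difference with its 95% confidence interval. Keep the z > 1 logistic analysis beside it. State in the same place which outcomes in the linear-and-logistic sentence take which model, so that the intended analysis of 6-week size is no longer open to two readings.

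The cost is a wording change and one regression on data already being collected, with no extra visits, staff or participants. There are two small downsides. It adds one more secondary analysis. A lower mean z-score is also not by itself a benefit, so it should be interpreted together with the proportion above z = 1 and the small-for-gestational-age results.
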